## Abstract

**Background:**

Tourniquet is currently widely used in total knee arthroplasty to reduce intraoperative blood loss. The academic view of tourniquet application in TKA is now in dispute. Some scholars argue that tourniquet may cause quadriceps injury and bring extra side effects, so they oppose the application of tourniquet. Others find that tourniquet application has no significant adverse impact on TKA patients. Regarding its advantages in reducing intraoperative blood loss, they advocate the regular application of tourniquet in TKA. Quadriceps injury is considered the main cause of tourniquet side effects. There are now many high-quality trials about tourniquet application in TKA but few of them concentrate on quadriceps morphology and function.

**Methods:**

A prospective, single-blind, randomized controlled trial will be adopted. The target sample is 130. Patients who meet the eligibility criteria will be randomly allocated to the tourniquet group and non-tourniquet group. The primary outcome is quadriceps thickness evaluated by ultrasound test. Secondary outcomes include quadriceps stiffness, rehabilitation outcomes, operation time, intraoperative and postoperative blood loss, blood transfusion rate, thigh circumference, VAS score, opioid consumption, d-dimer and C-reactive protein level in the serum, knee function score, postoperative satisfaction score, and complications.

**Discussion:**

This proposed study will contribute to improve evidence of tourniquet application in total knee arthroplasty. This will be a high-quality single-blind randomized controlled trial with a sufficient sample size and strict study design. It will investigate the effects of tourniquet application especially on the morphology and function of quadriceps in patients undergoing total knee arthroplasty and offer advice for tourniquet application in clinical practice.

**Trial registration:**

Chinese Clinical Trial Registry ChiCTR2000035097. Registered on 31 July 2020

## Background

Total knee arthroplasty (TKA) is currently considered the optimal treatment of severe knee osteoarthritis [1, 2]. Intraoperative and perioperative blood loss is quite considerable in TKA because a lot of osteotomy and soft tissue release is required. In order to decrease intraoperative blood loss and create a bloodless surgical field, tourniquet is now widely used in TKA [3, 4]. Its hemostasis function is accomplished by squeezing quadriceps to close lower limb vessels.

However, some scholars argue that tourniquet may have ischemia-reperfusion damage to the quadriceps [5, 6]. They find that tourniquets have no significant impact on decreasing perioperative blood loss but bring certain side effects such as pain, swelling, and deep vein thrombosis for TKA patients [5, 7], so they advocate to reduce or even avoid tourniquet application in TKA. Rames et al. [8] recently published the results from their retrospective study, which showed that patients without a tourniquet had less narcotic consumption and increased distance ambulated prior to discharge. Dong et al. [9] showed less pain and a larger range of motion in patients without a tourniquet. A meta-analysis conducted by Liu et al. [10] also found that the absence of tourniquet could significantly reduce postoperative pain and complication rate and, therefore, be beneficial to Enhanced Recovery After Surgery (ERAS).

In contrast, other scholars hold an opposite idea. Their studies find that tourniquets have no significant impact on postoperative outcomes in TKA patients [4, 11, 12]. Considering the bloodless surgical field and shorter operation time, they propose regular application of tourniquets in TKA. Nicolaiciuc et al. [11] found in a retrospective study that there was no significant difference in pain, narcotic consumption, and range of motion caused by tourniquet application. Furthermore, Jawhar et al. [13] conducted a randomized controlled trial. They introduced the method of a rope pulley isokinetic system and showed that tourniquet had little influence on quadriceps strength and function, patient satisfaction, and physical condition. McCarthy et al. [4] also found there was no significant difference in pain, range of motion, and average length of stay for TKA patients with or without a tourniquet.

Above all, there is no consensus on tourniquet application in TKA, and tourniquet-related side effects are considered relevant to quadriceps injury [14]. Therefore, we design this prospective single-blind randomized controlled trial to focus on tourniquet impact on quadriceps. With the assistance of ultrasonic and rehabilitation tests, we aim to evaluate the tourniquet impact of quadriceps morphology and function for TKA patients, along with operation time, blood management, limb swelling, postoperative pain, inflammatory process, postoperative satisfaction, and complications.

## Methods

### Study design

This study is a clinical randomized controlled trial of estimated 130 patients with knee osteoarthritis undergoing TKA in Peking University Third Hospital (Fig. 1). All patients are randomly divided into the tourniquet group and non-tourniquet group (65 patients each). A tourniquet is applied throughout the surgery in the tourniquet group. In the non-tourniquet group, a tourniquet is tied up but will not be inflated. The trial aims to compare clinical outcomes of TKA with and without a tourniquet. Single binding is performed in this trial which means that the patients are unaware of whether the tourniquets are used in their surgeries. The study will stop once the enrollment is completed.

**Fig. 1 Fig1:**
[figure not shown]
Flowchart of the study process

We assume the primary hypothesis of this trial is that quadriceps thickness in the tourniquet group is not less than that in the non-tourniquet group (non-inferiority study).

### Eligibility criteria and recruitment

The inclusion criteria for this trial are as follows:
Patients with primary knee osteoarthritisPlanning to operate unilateral primary total knee arthroplasty

The exclusion criteria are as follows:
Severe varus (> 25°) or valgus (> 20°) deformity of the kneeExtraarticular deformityPast medical history of knee surgery or knee infectionPrevious long-term consumption of anticoagulant drugs or complicated with the following diseases: renal insufficiency (Cr > 2.5), liver dysfunction, severe heart disease (or coronary stenting in the late 12 months), severe respiratory system diseases, previous venous thromboembolism history or high risk of thrombosis (genetic or acquired thrombosis diseases), blood coagulation dysfunction, the acquired thrombotic diseases, blood coagulation dysfunction, stroke, or malignant tumor historyPatients who refuse to sign the informed consent for any reason.

According to the eligibility criteria, a sample of 130 patients is included in this single-center trial. All participants enrolled in this study will receive cost-free postoperative rehabilitation tests and guidance. Post-trial cares such as health consultation and long-term review are also provided.

### Allocation and randomization

All participants who met the study inclusion and exclusion criteria are randomly assigned in a 1:1 ratio to the tourniquet and non-tourniquet groups by the method of random envelope. Prior to study initiation, an independent statistician will use the SAS 9.4 software (SAS Inc., Cary, NC, USA) to generate a blocked random number sequence in permuted blocks of 4 participants. The electronic data capture system automatically generates participant ID numbers in sequence, which are subsequently linked to tourniquet assignments at randomization. Both the participants’ ID numbers and their allocation groups (tourniquet or non-tourniquet) will then be sealed in an envelope. The scientific secretory of this trial is responsible for enrolling participants and assigning participants to intervention (Table 1).

**Table 1 Tab1:** Schedule of enrollment, interventions, and assessments

Time point		Study period									
		Enrollment	Allocation	Post-allocation							
				t1	t2	t3	t4	t5	t6	t7	t8
Enrollment	Eligibility screen	X									
	Informed consent	X									
	Randomization		X								
Interventions	Tourniquet group				X						
	Non-tourniquet group				X						
Assessments	Demographic data			X							
	Quadriceps thickness			X			X				
	Quadriceps stiffness			X			X				
	Isokinetic muscle strength test								X		
	3D gait analysis								X		
	Posture stability testing								X		
	Thigh circumference			X		X	X				
	VAS score					X	X	X	X		
	Opioid consumption						X				
	Knee function score			X						X	X
	Postoperative satisfaction score									X	X
	Operation time				X						
	Intraoperative blood loss				X						
	Perioperative blood loss						X				
	Blood transfusion rate					X	X	X			
	d-dimer			X		X	X				
	C-reactive protein			X		X	X				
	Complications					X	X	X	X	X	X

*t1* before the operation, *t2* in operation, *t3* 1 day after the operation, *t4* 3 days after the operation, *t5* 2 weeks after the operation, *t6* 6 weeks after the operation, *t7* 3 months after the operation, *t8* 1 year after the operation

Participants and researchers who offer ultrasound and rehabilitation evaluation will all be blinded to the group allocation. However, in case of any medical emergency in the study period, allocation will be unblinded to researchers and clinicians for further medical treatment.

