### Outcomes and measures

#### Preoperative measurements

Demographic information of all the patients is collected, including gender, age, height, weight, and BMI. Baseline outcomes including quadriceps thickness and stiffness, thigh circumference, knee function scores, hematocrit and hemoglobin level, d-dimer, and C-reactive protein level in the serum are evaluated before surgery but after randomization and allocation.

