### Data collection and management

All the data should be collected timely, correctly, and completely in the case report form. The stiffness and thickness of the quadriceps muscle are collected by ultrasound researchers. The isokinetic muscle strength tests, three-dimensional gait test, and balanced postures test are collected by rehabilitation researchers. The rest of the outcomes are collected by orthopedic researchers. All the data is stored in the database and processed by Microsoft Excel®.

The data management committee consisting of orthopedic surgeons, statisticians, and administrative staff is established to assess the progress of this study, so as to ensure the safety of study participants and to maintain the study’s scientific integrity.

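### Fixed, published blocks of 4 with one role both enrolling and assigning, and baseline placed after allocation, leave an avoidable risk of selective enrolment

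*Protocol article*

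**What the plan says.** All references are to the protocol article.

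- **Sequence** (Allocation and randomization). Participants are "randomly assigned in a 1:1 ratio to the tourniquet and non-tourniquet groups by the method of random envelope". The list is made in advance by an independent statistician, who will "generate a blocked random number sequence in permuted blocks of 4 participants". One block size is given.
- **Concealment** (same section). Participant IDs and "their allocation groups (tourniquet or non-tourniquet) will then be sealed in an envelope".
- **Who enrols and who assigns** (same section). "The scientific secretory of this trial is responsible for enrolling participants and assigning participants to intervention".
- **Order of events** (Preoperative measurements). Baseline thickness, stiffness, thigh circumference, knee scores and blood values "are evaluated before surgery but after randomization and allocation". Table 1 agrees: its preoperative visit, t1, stands under the post-allocation columns.
- **Blinding** (Allocation and randomization; Data collection and management). Participants and the ultrasound and rehabilitation assessors are stated to be blinded. Ultrasound researchers collect thickness and stiffness, and rehabilitation researchers collect the function tests. "The rest of the outcomes are collected by orthopedic researchers", and that group is not in the list of blinded roles.
- **Setting** (Eligibility criteria and recruitment; Baseline procedures; Trial status). There is one centre and one operating surgeon, and 84 of 130 participants had been recruited when the article appeared.

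**The concern.** Three stated features combine. The block is small and of constant size, the person who enrols also makes the assignments, and the assignment exists before any baseline value is taken.

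The first two bear on selection. A role that makes every assignment accumulates the history of the list. With that history and the block size, part of the list can be worked out ahead, so whom to enrol, or when, could depend on the coming arm. Blinded ultrasound does not protect against this, because the bias would lie in who enters each group. The primary test is an unadjusted Mann-Whitney test, and the supporting mixed model lists group, gender, age, height and weight. Selection related to quadriceps status would therefore pass into the primary comparison largely uncorrected.

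The third feature bears on measurement. A baseline taken by someone who may know the arm can be influenced by it. The article means to judge swelling by comparing thigh circumference before and after surgery between the groups, so a shifted baseline there would matter.

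The early allocation is also unnecessary. Under Intervention, the cuff is placed on every patient after anaesthesia and the groups differ only in whether it is inflated. No earlier step needs the assignment.

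**Working it through.** The article states no figure for predictability, so there is none to reproduce. The check asks how much of the list could be foreseen by someone who knows the block size, where blocks begin, and every earlier assignment.

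**Inputs.** Ratio 1:1 and block size 4 (Allocation and randomization); 130 planned and 84 recruited (Sample size estimation; Trial status).

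**Enumeration for blocks of 4.** There are 4!/(2!·2!) = 6 equally likely orders. An assignment is certain when one arm's two places are already used. Otherwise the best guess is the arm with more places left.

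| Position in block | Probability that it is certain | Probability that the best guess is right |
|---|---|---|
| 1 | 0 | 1/2 |
| 2 | 0 | 2/3 |
| 3 | 1/3 | 1/3·1 + 2/3·1/2 = 2/3 |
| 4 | 1 | 1 |

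- Share certain: (0 + 0 + 1/3 + 1)/4 = 33.3%.
- Share guessed correctly: (1/2 + 2/3 + 2/3 + 1)/4 = 70.8%, against 50% when the history or the block structure is unknown.

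**Counts.** 130 = 32 full blocks plus 2, so 32 × 4/3 ≈ 43 assignments would be certain over the whole trial. If all 84 recruited had been randomised, they fill 84/4 = 21 blocks. The remaining 130 − 84 = 46 are 11 full blocks plus 2, with 11 × 4/3 ≈ 15 certain assignments.

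**Would a larger fixed block be enough?** The same enumeration gives:

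| Fixed block size | Certain | Best guess right |
|---|---|---|
| 4 | 33.3% | 70.8% |
| 6 | 25.0% | 68.3% |
| 8 | 20.0% | 66.6% |

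A larger constant block helps only modestly. Who can see the earlier assignments, and whether the block sizes are known, matters more.

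**Which baselines are exposed?** Setting the blinding statement beside the list of who collects what:

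| Baseline item | Source | Exposed? |
|---|---|---|
| Quadriceps thickness, stiffness | Ultrasound researchers, stated blinded | No |
| WOMAC | Taken as reported by participants, stated blinded | Little |
| Haematocrit, haemoglobin, d-dimer, CRP | Laboratory values | Little |
| Thigh circumference | Orthopedic researchers, not listed as blinded | Yes, if they know the arm |
| Any examiner-rated part of KSS | Orthopedic researchers, not listed as blinded | Yes, if they know the arm |

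**The case against.** The strongest reply is that the article describes a reasonable concealment device and that the worst readings go beyond its text. An independent statistician makes the list, and the assignments are sealed. Much of this reply stands, and it removes several inferences that a reader might draw.

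- *That envelopes are opened before baseline.* The article gives the order, allocation and then baseline. It does not say when an envelope is opened or who then learns the group. A participant could be allocated with the envelope still sealed at t1. Custody and opening time are details that an article commonly leaves to the full protocol.
- *That the baselines in general are unblinded.* The primary outcome's baseline is measured by an assessor stated to be blinded. Baseline thickness is also not a listed covariate, and no change score is defined for the primary test, so a distorted baseline has little route into that comparison.
- *That the operating surgeon can steer recruitment.* This surgeon must see whether the cuff is inflated, but the article gives that surgeon no recruiting role. Consent is taken by a designated surgeon who is not identified as the one operating.
- *That upcoming assignments are simply predictable.* Two thirds are not certain even to a fully informed observer, and the article does not say that the secretary was given the block size.
- *That withdrawals before surgery will depend on the arm.* Participants are blinded, and nothing shows that anyone who could prompt such a withdrawal knows the arm.

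The reply does not remove the core. The fixed block, the joint enrolling and assigning role, and the order of allocation and baseline are stated procedures, not details lost in condensing. The secretary learns past assignments by making them, and the article itself disclosed the block size while places were still open.

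**Conclusion.** The concern holds in a limited, conditional form. For a person who knows the block size and all earlier assignments, one third of assignments are certain and 70.8% can be guessed, against 50% under full concealment. By the article's description, the scientific secretary has the assignment history, and the published text supplies the block size. Selective enrolment or timing is therefore an avoidable risk, and it reaches the primary comparison because the test is unadjusted and the supporting model does not list baseline thickness. The measurement risk is secondary: mainly thigh circumference and any examiner-rated KSS component, and only if those assessors know the arm.

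The percentages are upper limits. They assume known block boundaries and complete knowledge of the history, and bias follows only if someone acts on it. Nothing in the article shows that prediction occurred. The count of about 15 certain assignments still to come also assumes that the 84 recruited had all been randomised. The sample size is unaffected. This is an inexpensive improvement worth making, not a flaw that invalidates the design.

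**What to change.** For participants not yet randomised:

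1. Complete all t1 assessments before allocation, and correct Preoperative measurements and Table 1 to show this order.
2. Have existing theatre staff with no part in recruitment release the assignment after anaesthesia, just before the cuff would be inflated. The scientific secretary continues to enrol but no longer assigns.
3. Have the independent statistician regenerate the unused part of the list with randomly mixed block sizes (4 and 6, for example) and keep the sizes undisclosed.

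Steps 1 and 2 do most of the work. Step 3 alone would help less, as the figures for larger blocks suggest.

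The cost is a protocol amendment, notified as the article's own rules require, re-linking of IDs in the data capture system, and re-sealing of about 46 envelopes. The final group sizes may differ slightly: an unfinished block of 6 can leave a difference of 3. The present list can already leave a difference of 2, since 130 is not a multiple of 4. The change brings no benefit for the 84 already recruited. For them, the trial report should say when envelopes were opened, and who knew the block size and the earlier assignments.

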### Trial registration, ethics review, and informed consent

This trial is registered at the Chinese Clinical Trial Registry (registration number: ChiCTR2000035097) and approved by the Peking University Third Hospital Medical Science Research Ethics Committee (Registration number: M2020290).

All the participants sign the informed consent before the trial. An appointed surgeon is responsible for taking informed consent and explain all the intended benefits and risks of tourniquet use to every participant. Consent of participant data and biological specimens are also included in the informed consent. Blood specimens in this study will be disposed after testing and will not be used for genetic analysis or used in other studies. Every participant will be represented by an ID number, and personal information such as name, address, and telephone number will be kept confidential out of Peking University Third Hospital before, during, and after the study. The trial is conducted with the Declaration of Helsinki.

### Baseline procedures

All patients are operated on by the same surgeon. This surgeon has more than 15 years of TKA experience including non-tourniquet TKA and operates at least 300 TKAs per year. All the surgeries are operated by conventional tools. Medial patellar skin incision, medial parapatellar arthrotomy, and measured resection are adopted in all patients. The patella is resurfaced and denervated by hand saw instead of patella replacement. Posterior stabilized implants (Legion from Smith and Nephew, Memphis, TN, USA) are selected.

Perioperative treatments are the same in both groups. Patients all receive intraspinal anesthesia or general anesthesia along with controlled hypotension which is defined as a reduction of the systolic blood pressure to less than 90 mmHg and a reduction of mean arterial pressure (MAP) to less than 65 mmHg or a 30 to 40% reduction of baseline MAP. Before the surgery, all the patients receive a single-time femoral nerve block instead of a continuous femoral nerve block to reduce postoperative pain. Tranexamic acid is used before skin cutting (1 g ivgtt) and before skin suture (1 g ivgtt). Thromboprophylaxis is done with sodium enoxyeparin, 4000 IU per day, starting 12 h after surgery. After the surgery, no femoral block tube or drainage tube is reserved.

Compression of elastic bandage to the surgery limb after suture (removed 24 h after surgery) and active and passive ankle pump training (start immediately after surgery) are adopted in both groups. No patients use continuous passive motion machine. Patients stay in a rest position with the knee in full extension, and they start active and passive rehabilitation training guided by a physical therapist 12–24 h after surgery (local ice compress for 15 min after each training). Patients are encouraged to perform isometric quadriceps exercise and walk with a walker on the first postoperative day. Range of motion (ROM) exercises are performed twice a day in the 6-week period. At 4–6 weeks after surgery, patients are encouraged to walk without aid gait.

The standard plan of postoperative analgesia is also the same in the two groups. Flurbiprofen Axetil (100 mg bid ivgtt) is regularly used for all patients for 2 days after surgery (patients with sulfonamides allergy use parecoxib sodium 40 mg bid ivgtt). If pain control is not satisfying, tramadol or oxycodone (1 tablet once, po) will be used.

### Intervention

A tourniquet is tied to patients in both groups after anesthesia so that tourniquet application is blind to patients. Tourniquet in the tourniquet group is inflated to a standard pressure of (260 ± 10) mmHg (from skin cutting to skin suture). Tourniquet in the non-tourniquet group will not be inflated. There is no concomitant intervention in this study. Proper treatment and care of participants’ combined diseases are allowed. Extra use of analgesic, anticoagulant, and anti-anemia drugs out of the study protocol is prohibited. Participants will be excluded from the trial if these drugs are necessary.

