##### Other secondary outcomes

Other secondary outcomes are also evaluated, including operation time, intraoperative and postoperative blood loss, blood transfusion rate, thigh circumference, VAS score, opioid consumption, d-dimer and C-reactive protein level in the serum, knee function score, postoperative satisfaction score, and complications.

Operation time, which also means tourniquet application time, is evaluated as well. It is defined as the time from skin cutting to the skin suture, and it is accurate to minutes.

Intraoperative blood loss and postoperative blood loss (3 days after surgery) are also evaluated in this trial. Hematocrit level is tested before surgery and 3 days after surgery. Calculating methods are as follows: intraoperative blood loss = intraoperative fluid intake volume + intraoperative irrigation volume + gauze infiltration volume (ml); postoperative blood loss = total blood loss − intraoperative blood loss; total blood loss is calculated by gross linear equation [15]: total blood loss=preoperative blood volume (PBV) ×(preoperative Hct – postoperative Hct)/average Hct, average Hct=(preoperative Hct + postoperative Hct)/2; preoperative blood volume is calculated by Nadler equation [16]: PBV = K1 × height (m)3 + K2× weight (kg) + K3 (for male: K1 = 0.3669, K2 = 0.03219, K3 = 0.6041; for female, K1 = 0.3561, K2 = 0.03308, K3 = 0.1833).

Blood transfusion and transfusion volume after surgery are recorded, and blood transfusion rate is calculated in 1 day, 3 days, and 2 weeks after surgery. Hemoglobin level is tested before surgery as well as 1 day and 3 days after surgery. Blood transfusion is done only if Hb level is lower than 70 g/L, or Hb level is between 70 and 90 g/L with symptoms of anemia like weakness and palpitations. The standard transfusion solution is 400 mL of suspended erythrocyte each time, with a reexamination of blood routine on the second morning.

The circumference of the upper third of the affected thigh is measured with a tape 1 day before surgery as well as 1 day and 3 days after surgery, with an accuracy of 0.1 cm. The swelling degree of quadriceps can be reflected by comparing the circumference in the two groups preoperatively and postoperatively.

VAS scores of the thigh and knee are separately evaluated at 1 day, 3 days, 2 weeks, and 6 weeks after surgery. Opioid consumption (in morphine equivalence) in 3 days after surgery is also recorded to further evaluate postoperative pain.

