d-dimer and C-reactive protein (CRP) level in the serum is tested before surgery as well as 1 day and 3 days after surgery to reflect ischemia-reperfusion injury and inflammatory reaction. Complications of patients in both groups such as deep vein thrombosis, hematoma, and anemia are recorded at 2 weeks, 6 weeks, 3 months, and 12 months after surgery.

The knee function score KSS (Knee Society Score) and WOMAC (Western Ontario and McMaster Universities Osteoarthritis Index) are also evaluated before surgery as well as 3 months and 1 year after surgery. Both of the scores are widely used knee function scores worldwide. Their validity and reliability have been verified many times [17–22].

Postoperative satisfaction score is recorded 3 months and 1 year after surgery. It ranges from 1 to 5 points to reflect patients’ satisfaction rate of surgery and recovery. (1 = very dissatisfied, 2 = not satisfied, 3 = neutral, 4 = satisfied, 5 = very satisfied)

In addition, all complications such as deep venous thrombosis, skin vesicle, subcutaneous ecchymosis, and hematoma will be recorded in the study period.

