### Statistical analysis

The statistician who conducted the analysis is blinded to the group allocation. Summary statistics are used to describe the participant characteristics of the trial groups at baseline in the intention-to-treat (ITT) analysis set. The missing data of quadriceps thickness and stiffness is imputed by the multiple imputation method. The results of multiple imputation data are used as a type of sensitivity analysis for comparing primary outcomes between the groups.

For primary outcomes comparison, the ITT analysis is performed to evaluate the differences between the groups, and effective analysis population (EAP) and per-protocol (PP) analyses are also performed for sensitivity assessment. The primary outcomes do not follow the Gaussian distribution and are presented as median (IQR) and tested by the Mann-Whitney *U* test. Bonferroni correction is used to reduce the significance level. The means (95% CIs) of the between-group differences of the medians are calculated by the bootstrap method (1000 replications). The generalized linear mixed models (GLMM) are also performed for the primary endpoint, including group, gender, age, height, and weight as fixed covariates.

For comparing the secondary and exploratory endpoints, continuous data are presented as means (SDs) or medians (IQRs) as appropriate. The secondary endpoints are analyzed by the linear mixed model (LMM), adjusted for gender, age, height, weight, and other covariates. The correlation type of different measurement time points is assumed as the first-order autocorrelation in the LMM. Exploratory endpoints are compared by the Mann-Whitney *U* test, and the significance level is submitted to Bonferroni correction.

For safety endpoints, categorical data are presented as counts and percentages and tested by the Pearson’s chi-square test or Fisher’s exact test. The 95% CIs of absolute risk differences between the groups are calculated by the Newcombe-Wilson Score method. All statistical analyses are conducted with the statistical package SPSS, V.18.0 (SPSS Inc.) and the R 3.4.0 software. Besides Bonferroni correction, statistical significance is defined as *p* < 0.05with two-sided testing.

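### Participants who need extra analgesic, anticoagulant or anti-anaemia drugs are removed after randomisation, which conflicts with the ITT analysis and selects the data, mainly for secondary and later outcomes

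*Protocol article*

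**What the plan says.** Protocol article, Intervention: "Extra use of analgesic, anticoagulant, and anti-anemia drugs out of the study protocol is prohibited", followed directly by "Participants will be excluded from the trial if these drugs are necessary". The exclusion is from the trial, not from one analysis set.

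Statistical analysis: "For primary outcomes comparison, the ITT analysis is performed to evaluate the differences between the groups". In addition, "effective analysis population (EAP) and per-protocol (PP) analyses are also performed for sensitivity assessment". On missing values: "The missing data of quadriceps thickness and stiffness is imputed by the multiple imputation method". The imputed results serve as a sensitivity analysis.

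Preoperative measurements: baseline values "are evaluated before surgery but after randomization and allocation". A need for drugs beyond the regimen therefore arises after allocation, and mainly after surgery.

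Other secondary outcomes: "Opioid consumption (in morphine equivalence) in 3 days after surgery is also recorded to further evaluate postoperative pain". VAS is scored up to 6 weeks. "Complications of patients in both groups such as deep vein thrombosis, hematoma, and anemia are recorded" at visits up to 12 months.

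The Background lists pain, swelling and deep vein thrombosis among the side effects that some authors attribute to the tourniquet. The section on adverse events has all adverse events recorded and reported, and asks for the reasons when a participant discontinues or deviates. It does not say that an excluded participant continues to be followed.

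**The concern.** An ITT comparison needs every randomised participant to be followed and counted in the allocated arm. Here the reason for removal lies close to the outcomes: more pain leads to more analgesic, a thrombosis to an anticoagulant, anaemia to an anti-anaemia drug. If the tourniquet affects any of these, the arms lose different numbers and different kinds of patients, and those who remain are no longer a randomised comparison.

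The intervention is a single operation. Exclusion after surgery therefore cannot mean stopping treatment. It can only end follow-up or remove data. What would be lost is VAS, opioid consumption, the 6-week function tests, KSS and WOMAC, satisfaction and later complications. For these the article states no recovery, because the multiple imputation it describes covers only thickness and stiffness. Thickness on day 3 is at risk only for participants excluded before that scan.

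**Working it through.** **1. The plan's own figure.** Inputs from Sample size estimation: SD 0.5 cm (non-tourniquet) and 0.6 cm (tourniquet), equal means of 3.1 cm, margin 0.31 cm, one-sided α 0.025, power 80%.
- Average variance = (0.5² + 0.6²)/2 = 0.305, SD 0.552.
- Normal approximation: n = 2 × 0.305 × (1.96 + 0.8416)² / 0.31² = 49.8, so 50 per group.
- Noncentral t: power 0.794 at 50 and 0.802 at 51. The stated 51 per group is reproduced.

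No stated figure depends on the exclusion rule. The article gives no exclusion rate, so the sizes below are illustrations under stated assumptions.

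**2. An outcome that itself triggers exclusion (such as pain).** Assume a normal outcome with SD 1, a true difference of 0.5 (tourniquet worse) and one removal threshold c for both arms. The mean of those retained in an arm with mean μ is μ − φ(c − μ)/Φ(c − μ).

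| Controls excluded | c | Tourniquet excluded | Retained means (T, C) | Difference retained |
|---|---|---|---|---|
| 5% | 1.645 | 12.6% | 0.263, −0.109 | 0.37 |
| 10% | 1.282 | 21.7% | 0.124, −0.195 | 0.32 |
| 20% | 0.842 | 36.6% | −0.094, −0.350 | 0.26 |

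No assumed correlation is needed here, because trigger and outcome are the same quantity.

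**3. Day-3 thickness.** Put the true difference exactly at the margin, −0.31 cm. Let the latent need for extra drugs have correlation ρ with thinner muscle, and let a fraction e of an arm be excluded before the scan.
- Upward shift of the retained mean in an arm = SD × ρ × k(e), with k(e) = φ(z)/(1 − e) and z the 1 − e normal quantile. k(5%) = 0.109, k(10%) = 0.195, k(20%) = 0.350.
- Bias = tourniquet shift − control shift.
- SE = √((0.25 + 0.36)/51) = 0.109 cm, ignoring the small loss of variance among those retained.
- False non-inferiority rate = 1 − Φ(1.96 − bias/SE).

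Worked case, 20% vs 10% and ρ = 0.5: 0.6 × 0.5 × 0.350 = 0.105; 0.5 × 0.5 × 0.195 = 0.049; bias 0.056 cm; rate 1 − Φ(1.96 − 0.514) = 7.4%.

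| Excluded, tourniquet vs control | ρ | Bias (cm) | False non-inferiority rate |
|---|---|---|---|
| 20% vs 10% | 0.5 | +0.056 | 7.4% |
| 10% vs 5% | 0.3 | +0.019 | 3.7% |
| 5% vs 5% | 0.5 | +0.005 | 2.8% |
| 20% vs 10% | −0.5 | −0.056 | 0.7% |
| 10% vs 20% | 0.5 | −0.029 | 1.3% |

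The nominal rate is 2.5%. The last two rows reverse the correlation and the exclusion rates in turn, and the error then falls below nominal.

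**The case against.** A reader might infer that the rule pushes the primary comparison towards non-inferiority. The documents do not support that. It requires both more exclusions with the tourniquet and thinner muscle in those excluded. Thickness is measured 3 days after surgery, when the protocol itself looks for quadriceps swelling, so more injured muscle could measure thicker. One trigger is anaemia, and the article credits the tourniquet with less intraoperative bleeding while calling its effect on total loss unsettled. Exclusions for anaemia could therefore be more frequent without it. This objection stands, and the last two rows of the table show what it does to the error rate.

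A reader might also infer that thromboses and anaemia go uncounted. All adverse events are to be recorded, so the event that triggers exclusion may well be captured. A thrombosis first seen on the day-3 ultrasound does not cost that day's thickness measurement. Only later events and assessments are at risk.

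Nor is opioid consumption capped by design. Tramadol or oxycodone for unsatisfactory pain control is within the protocol and triggers no exclusion, and no total limit is stated.

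Finally, separate ITT, EAP and PP analyses suggest that deviators may be meant to stay in the ITT set, whose definition may sit in a fuller document. That is a possible intention, but the sentence in Intervention says otherwise and does not confine exclusion to the PP set. Multiple imputation softens the loss of thickness and stiffness, but only as a sensitivity analysis.

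**Conclusion.** The conflict between Intervention and Statistical analysis is in the text and needs no assumption. Followed as written, the rule removes randomised participants for reasons tied to compared outcomes and leaves selected data.

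The main damage is to secondary and later outcomes. Where the outcome drives exclusion at a common threshold, a real difference shrinks; in the illustration 0.5 becomes 0.37 to 0.26 when 5% to 20% of controls leave. For day-3 thickness the effect is indirect and its sign unknown, with an illustrated false non-inferiority rate from about 1% to about 7%. The exclusion rates and correlations behind these figures are assumed, so they show what could happen and do not estimate this trial's error.

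**What to change.** Reconcile Intervention with Statistical analysis by replacing the exclusion sentence with one to this effect: use of such drugs outside the protocol is recorded as a protocol deviation; the participant completes all scheduled assessments and is analysed in the randomised arm in the ITT set; only the PP set leaves the participant out.

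The article reports 84 participants already recruited and does not say whether any were dropped under this rule. If any were, recover their outcomes where consent allows.

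The cost is a one-sentence amendment and the completion of visits already on the schedule. Assessments that were never made cannot be recovered at analysis, so the change is worth most while follow-up is still running. It takes no position on which drugs are given.
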